#### Dispensing of study medications

After administration, syringes should be properly disposed, per procedure for a Schedule III drug product, and per applicable federal, state and local regulations. If the XRB dose is left at room temperature for longer than seven days, it should be discarded.

#### Enhanced treatment-as-usual: patient navigator

All study participants will be given access to enhanced patient navigation, beyond what is currently offered by the jail (a single follow-up immediately following release). The study will provide an enhanced PN to facilitate their return to the community and to encourage continued participation in MOUD treatment. This approach has shown promising effects for adults leaving prison [10]. The PN from this project will collect locator data from the participant prior to release and attempt to contact the participant at 30, 60, and 90 days after the discharge date. The focus of the PN will be to (1) ask if there are any re-entry barriers that need to be addressed, and (2) encourage ongoing MOUD engagement in the community. The PN will endeavor to reach all participants at least one-time at each follow-up timepoint and will make follow-up contacts as is relevant.

#### Participant withdrawal

Participants are free to withdraw from the study at any time upon verbal request. An investigator may discontinue or withdraw a participant from the study if any clinical adverse event (AE), laboratory abnormality, or other medical condition or situation occurs such that continued participation in the study would not be in the best interest of the participant.

Subjects who sign the informed consent form and are randomized but are not assigned to a study condition (i.e., initiate/continue treatment relevant to their study arm) may be replaced. Subjects who sign the informed consent form and are randomized and successfully assigned to a study condition, and subsequently discontinue from the study, will not be replaced.

Participants in either treatment group that choose to drop out of the study during their incarceration will be transitioned back to the standard of care at facility. Participants who drop out from the study will no longer be contacted, receive patient navigation services, or be followed for study purposes.

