**Methods/study design:**

In this 3-year randomized controlled trial, we will identify and recruit 200 incarcerated adults with OUD who are receiving sublingual buprenorphine (SLB) or tolerate a SLB test dose and randomize them to receive extended release buprenorphine (XRB) (*n* = 100) or to remain on SLB (*n* = 100) while in custody. Study participation will continue through their pre-trial time in jail (up to 6 months) or until they are sentenced or released. Community treatment will then be tracked for 90 days following release. In addition to collecting data on XRB uptake in jail, we will assess (1) the percentage of XRB and SLB study participants leaving jail with a clinically active dose of buprenorphine in their system, (2) 90- day post-release MOUD continuation, (3) levels of buprenorphine diversion while in custody, and (4) recidivism and death (90 days). “Clinically active” is defined as receiving XRB within the past 28 days or SLB in the past 24 h.

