#### Random assignment

Randomization of eligible participants will occur within one week after screening. A randomization module has been created on REDCap, using a 1:1 permuted block design. Study assignment is unblinded. Participants and medical staff will be notified of the study arm assignment. It is anticipated that screening, the consent process, randomization, and treatment induction will likely occur within a 5-day window. While randomization to the experimental condition will not guarantee XRB induction, every practical effort will be made to induct participants onto XRB prior to release. It is, however, the nature of the unsentenced population that release dates are unpredictable. The percentage of participants in the experimental condition who do initiate XRB prior to release will be an important implementation finding of this project.

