## Results/hypotheses

### Planned analyses

The approach for testing the primary hypothesis— that administering XRB to pretrial detainees will result in a significantly higher proportion of participants being released with a clinically active dose of buprenorphine in their system than will SLB (TAU) participants— will use generalized linear models with a log-binomial link to generate risk ratios for the study groups. Outcome measures for the secondary outcomes include rates of enrollment in community MOUD following release from jail. We will also assess group differences in the infractions for diversion and recidivism. Differences across treatment arms (e.g., disciplinary infractions) will be assessed using generalized linear models depending on the nature of the outcome. In the case where there are repeated measurements for each individual (e.g., buprenorphine treatment continuity at X, Y, Z months), mixed effect models will be used with participant-level random effects.

This study is powered to detect a medium effect size corresponding to a risk ratio of 1.34 (OR = 2.4), assuming 75% are released from jail with a clinically active dose of buprenorphine in their system in the XRB condition, a two-tailed test, and a power of 0.80. Because the desired outcome is expected to be rare under the SLB condition, we also consider the precision of the primary outcome prevalence estimate under the XBR condition given the total sample size (*n* = 200). With *n* = 100 participants in the XBR condition and 0.75 expected for the prevalence of the primary outcome, the 95% confidence interval width is 0.168 (i.e., 0.657–0.825).

Retention-in-study-medication-treatment will be tracked using administrative data. We will make every attempt to confirm suspected deaths, cause-of-death, and relevant collateral data through participant contacts, public information, and public death data.

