We will use a modified intention-to-treat (mITT) approach. The primary analysis sample will be participants randomized and released to the community. Clinical trials in the criminal legal system usually see a small rate of randomized participants initially planning for release, then sentenced, transferred, or otherwise incarcerated for longer periods of time due to unanticipated post-randomization factors independent of the study. This effectively renders the now randomized participant ineligible, as they are unable to leave the jail and continue treatment in the community. Thus, participants not released to the community as planned will be excluded from the analysis of the primary outcome. Participants who are not released to the community do not enter the risk set for outcomes that can only be observed at release or in the community after release. While we do not expect arm differences in the probability of release to the community, we will examine this as an exploratory outcome descriptively and with a Fisher’s exact test in intent-to-treat (ITT) analysis. In other ITT analyses, the approach will be outcome-dependent. For the outcomes of buprenorphine in a participant’s system at release and participation in MOUD treatment following release, these participants would be coded as No. For buprenorphine diversion during incarceration, these cases need no special treatment since the outcome does not depend on release. For rearrests, ITT analysis would code these participants as not rearrested. In all modified intent-to-treat (mITT) or per protocol analysis of outcomes observed at or after release to the community, participants not released to the community will be excluded. We expect this to occur among fewer than 5% of all participants who are randomized. Secondary analyses will examine all randomized participants (ITT) and participants both inducted and released as planned (per protocol). Sensitivity analyses will examine the effect of competing risks (i.e. incarceration or death) after release on the primary outcomes.

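### The dropout rule ends all study follow-up, although the primary and ITT analysis sets include dropouts and the outcomes come from records that could still be read

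*Protocol article*

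**What the plan says.** Under Participant withdrawal, the protocol article says: "Participants who drop out from the study will no longer be contacted, receive patient navigation services, or be followed for study purposes". The section covers participants in either arm who choose to leave, and they return to the jail's standard care. It also allows an investigator to withdraw someone from the study, not only from the drug, for an adverse event or laboratory abnormality. It does not mention outcome records.

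Planned analyses defines the primary, modified ITT sample as participants who were randomised and then released to the community. It adds: "Secondary analyses will examine all randomized participants (ITT", followed by a per-protocol set of those inducted and released. The instruction to code certain participants as No in the ITT analysis applies only to those not released. The same section says: "Retention-in-study-medication-treatment will be tracked using administrative data".

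Table 1 and the outcome sections name the sources:
- dosing and release protection: the jail medical record (CorEMR), with the offender management system (OMS) for release
- diversion: OMS and the security unit (IPS)
- community treatment: clinic records
- recidivism: criminal-justice (CJIS) records
- death: vital statistics, the national death index and public sources

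**The concern.** The withdrawal sentence lists contact, navigation and follow-up as three separate things that stop. The natural reading of the third is that outcome data stop too. If site staff apply it that way, outcomes will be missing for people whom the analysis section counts, including in the primary set, because a dropout who is later released belongs there. An analysis plan written afterwards cannot recover data that the protocol told staff not to collect.

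The loss could also be unequal between arms. Assignment is open. A participant on sublingual buprenorphine (SLB) is already on treatment as usual, so leaving changes medication mainly for someone assigned to XRB. Adverse-event withdrawal also bears more on a newly started drug. If XRB dropouts do worse than the rest of their arm and are left out, XRB looks better than it is. Deaths and re-incarcerations among dropouts would go uncounted as well.

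**Working it through.** **Inputs from the document.** The Abstract gives the arm sizes: "randomize them to receive extended release buprenorphine (XRB) (*n* = 100) or to remain on SLB (*n* = 100) while in custody". Planned analyses gives the effect, "risk ratio of 1.34 (OR = 2.4", the XRB rate, "assuming 75% are released from jail with a clinically active dose", and the test, "a two-tailed test, and a power of 0.80".

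**Assumptions.** Alpha is not stated, so 0.05 is assumed. No dropout rate is stated. The only loss figure, under 5%, concerns participants not released. Dropout of 5–20% is used for illustration, with 10% as the worked case.

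**Step 1: reproduce the plan's figure.**
- Implied SLB rate: 0.75 / 1.34 = 0.560.
- Odds ratio: (0.75/0.25) / (0.560/0.440) = 2.36, which rounds to the stated 2.4.
- Power for two proportions with 100 per arm: 0.813. With a Wald test on the log odds ratio it is 0.800.

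The stated 0.80 reproduces, so the sample size is not in dispute.

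**Step 2: exclude dropouts, with loss in XRB only.** Let d be the share of the XRB arm that drops out and r the proportion of those dropouts who would have met the primary outcome. Then:

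observed XRB rate = (0.75 − d·r) / (1 − d); observed RR = that rate / 0.560.

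For the false-positive rate, both arms are set to a true 0.56. The observed XRB rate is then (0.56 − d·r) / (1 − d), compared with 0.56 using 90 versus 100 participants in a two-sided normal test.

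With d = 0.10:

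| r among dropouts | Observed XRB rate | Observed RR | XRB rate under no effect | False-positive rate |
|---|---|---|---|---|
| 0.75 (same as arm) | 0.750 | 1.34 | – | – |
| 0.56 (SLB rate) | 0.771 | 1.38 | 0.560 | about 5% |
| 0.30 | 0.800 | 1.43 | 0.589 | about 7% |
| 0 (none active) | 0.833 | 1.49 | 0.622 | about 14% |

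Across d = 5% to 20%, the RR runs from 1.36 to 1.43 at r = 0.56 and from 1.38 to 1.54 at r = 0.30.

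**Step 3: code dropouts as No instead.** The observed RR becomes (0.75 − d·r) / 0.560. With d = 0.10 and r = 0.56 this is 0.694 / 0.560 = 1.24, so the bias now runs against XRB.

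**Step 4: power, leaving bias aside.** Losing 10% from both arms lowers power from 0.813 to 0.770. Losing 10% from XRB only lowers it to 0.790.

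**Step 5: compare the provisions.** The withdrawal section stops follow-up of dropouts. The analysis section includes them in two analysis sets and gives a coding rule only for a different group. The data-source table shows that most outcomes need no contact. Only the confirmation of suspected deaths draws partly on participant contacts, alongside public data.

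**The case against.** The sentence does not mention records. It could mean only that active follow-up ends, and Planned analyses says medication retention is tracked administratively. The consent form and any full analysis plan are not shown, and either may settle the matter. In a prisoner population with withdrawal on verbal request, ending follow-up on request is also a defensible protection. These points stand in part. They make the ambiguity worth resolving, but they do not remove it, because a stated rule and a stated analysis set disagree. Ending follow-up when a participant asks for exactly that is compatible with continuing record capture for those who do not.

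Three stronger readings are tempting and are not supported.

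- *The ITT analysis is impossible.* Even on the strict reading, a coding or imputation rule would allow one. It could not rest on observed outcomes for everyone randomised.
- *The losses will be XRB refusers.* The rule covers either arm, and willingness to accept either assignment is an entry criterion. Leaving also costs participants in both arms the enhanced navigator. Under Random assignment, XRB induction is not guaranteed and non-initiation is reported as a finding. The primary set does not require induction. Declining or missing the injection is therefore not in itself dropping out.
- *A dropout is a primary-outcome failure.* The Abstract counts SLB within 24 hours of release, or XRB within 28 days, as clinically active. Someone who returns to SLB, or who leaves after a recent injection, can succeed. The RR of 1.49 and the false-positive rate of about 14% need every dropout to have no active buprenorphine.

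**Conclusion.** The point holds as a conflict between the withdrawal rule and the analysis sets, and it reaches the primary analysis as well as the ITT analysis. Most of the loss is avoidable because the outcomes are record-based. Differential loss towards XRB is plausible but is an inference, since no dropout rate or arm split is documented.

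The size depends on assumptions that the document does not supply. At an assumed 10% dropout confined to XRB, exclusion moves the RR from 1.34 to between 1.34 and 1.43 for dropout success rates from 0.75 down to 0.30, with 1.49 as the extreme. With no true effect, the false-positive rate is about 5% at 0.56 and 7% at 0.30, rising to about 14% only in that extreme. Coding dropouts as failures reverses the direction. The result therefore turns on a rule that the article does not give, and collecting the records would largely remove that dependence.

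**What to change.** In the protocol and the consent form, separate three levels: stopping the assigned medication, stopping contact and navigation, and withdrawing permission to use records. At the first two levels, keep capturing all record-based outcomes, including death and recidivism. Stop only when permission for records is itself withdrawn. Apply the same separation when an investigator withdraws a participant.

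Analyse these participants in their randomised arm in both the modified ITT and ITT sets. For those who withdraw permission for records, state how they are handled in each set and add a sensitivity analysis over a range of dropout success rates. Report withdrawals by arm and reason.

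The cost is a protocol and consent amendment with IRB review. No visits are added, because the record extractions are already planned.

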#### Subject payments

The study will provide non-coercive monetary incentives to participants. Participants will receive a letter, placed among their personal belongings that will be returned upon release from MJHOC, with the study’s contact information and be paid retroactively ($40). Following release, the participant will contact study staff who will coordinate the provision of payment to the participant.

## Results/hypotheses

### Planned analyses

The approach for testing the primary hypothesis— that administering XRB to pretrial detainees will result in a significantly higher proportion of participants being released with a clinically active dose of buprenorphine in their system than will SLB (TAU) participants— will use generalized linear models with a log-binomial link to generate risk ratios for the study groups. Outcome measures for the secondary outcomes include rates of enrollment in community MOUD following release from jail. We will also assess group differences in the infractions for diversion and recidivism. Differences across treatment arms (e.g., disciplinary infractions) will be assessed using generalized linear models depending on the nature of the outcome. In the case where there are repeated measurements for each individual (e.g., buprenorphine treatment continuity at X, Y, Z months), mixed effect models will be used with participant-level random effects.

This study is powered to detect a medium effect size corresponding to a risk ratio of 1.34 (OR = 2.4), assuming 75% are released from jail with a clinically active dose of buprenorphine in their system in the XRB condition, a two-tailed test, and a power of 0.80. Because the desired outcome is expected to be rare under the SLB condition, we also consider the precision of the primary outcome prevalence estimate under the XBR condition given the total sample size (*n* = 200). With *n* = 100 participants in the XBR condition and 0.75 expected for the prevalence of the primary outcome, the 95% confidence interval width is 0.168 (i.e., 0.657–0.825).

Retention-in-study-medication-treatment will be tracked using administrative data. We will make every attempt to confirm suspected deaths, cause-of-death, and relevant collateral data through participant contacts, public information, and public death data.

We will use a modified intention-to-treat (mITT) approach. The primary analysis sample will be participants randomized and released to the community. Clinical trials in the criminal legal system usually see a small rate of randomized participants initially planning for release, then sentenced, transferred, or otherwise incarcerated for longer periods of time due to unanticipated post-randomization factors independent of the study. This effectively renders the now randomized participant ineligible, as they are unable to leave the jail and continue treatment in the community. Thus, participants not released to the community as planned will be excluded from the analysis of the primary outcome. Participants who are not released to the community do not enter the risk set for outcomes that can only be observed at release or in the community after release. While we do not expect arm differences in the probability of release to the community, we will examine this as an exploratory outcome descriptively and with a Fisher’s exact test in intent-to-treat (ITT) analysis. In other ITT analyses, the approach will be outcome-dependent. For the outcomes of buprenorphine in a participant’s system at release and participation in MOUD treatment following release, these participants would be coded as No. For buprenorphine diversion during incarceration, these cases need no special treatment since the outcome does not depend on release. For rearrests, ITT analysis would code these participants as not rearrested. In all modified intent-to-treat (mITT) or per protocol analysis of outcomes observed at or after release to the community, participants not released to the community will be excluded. We expect this to occur among fewer than 5% of all participants who are randomized. Secondary analyses will examine all randomized participants (ITT) and participants both inducted and released as planned (per protocol). Sensitivity analyses will examine the effect of competing risks (i.e. incarceration or death) after release on the primary outcomes.

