## Methods

### Overview of study design

This three-year research project will recruit 200 participants at the Middlesex Jail and House of Correction (MJHOC). The two-group randomized trial will assess the potential benefits of offering XRB to pre-trial detainees. Participating pre-trial detainees receiving SLB will be randomized 1:1 to transition to XRB as soon as possible or remain on SLB during their jail term (or up to six months). Per usual treatment for MOUD recipients at the jail, all efforts will be made to refer participants to receive MOUD treatment in the community upon release. We will compare (1) the percentages of XRB and SLB participants leaving jail with a clinically active dose of buprenorphine in their system, (2) infractions for diverting buprenorphine while incarcerated, (3) community MOUD intake and retention, and (4) 90-day recidivism or death. The final three months of the study will be devoted to data cleaning and analysis, study close out, preparation of manuscripts, and dissemination.

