#### Secondary and tertiary outcome measures

The secondary outcome measure is MOUD continuation in the community. This outcome will be based on community clinic records indicating admission and retention at 90-days following release, measured as the number of SLB doses or XRB injections received in the community. Tertiary outcome measures involve a range of incidents including death, diversion, disciplinary actions, as well as recidivism outcomes at 90 days post release. Recidivism will be defined as arraignments, types of charges/offenses, incarcerations, and convictions. Data will be acquired through the jail from Criminal Justice Information Services (CJIS) records.

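### The one named secondary outcome, MOUD continuation in the community, is a dose count in the outcome section, an enrolment rate and a placeholder continuity measure in the analysis section, and a Yes/No in the ITT rule

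*Protocol article*

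**What the plan says.** The Protocol article describes community treatment after release in several places.

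- **Abstract, Methods/study design:** one of four items to be assessed is "90- day post-release MOUD continuation", with community treatment tracked for 90 days.
- **Overview of study design:** the arms are compared on "community MOUD intake and retention".
- **Secondary and tertiary outcome measures:** "The secondary outcome measure is MOUD continuation in the community". The basis is given next: "This outcome will be based on community clinic records indicating admission and retention at 90-days following release". The metric follows: "measured as the number of SLB doses or XRB injections received in the community".
- **Planned analyses, first paragraph:** "Outcome measures for the secondary outcomes include rates of enrollment in community MOUD following release from jail". Mixed models are then proposed for repeated measurements, with the example "buprenorphine treatment continuity at X, Y, Z months".
- **Planned analyses, mITT/ITT paragraph:** participants not released to the community are given a value for "participation in MOUD treatment following release, these participants would be coded as No".
- **Table 1:** community MOUD enrolment over 90 days, with number of appointments, medication type and dose amount as sub-items.

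**The concern.** The outcome section uses the singular and so commits the trial to one secondary outcome. The text then gives that outcome four forms: a count, an enrolment proportion, a repeated continuity measure without time points, and a binary indicator. An article may leave detail to a full protocol or analysis plan. Here, however, the article states several definitions and they do not agree.

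Three things are at stake. Each form needs a different model, so the analysis of the secondary outcome is not determined. Assignment is unblinded, so a choice among forms left open until data are seen is a weakness even if nobody intends to exploit it. And the one metric that is spelled out, the dose or injection count, would mislead if applied literally, because the two formulations are given at very different frequencies and other MOUD is not counted at all.

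**Working it through.** The plan gives no power, sample size or expected rate for this outcome, so there is no figure to reproduce for it. Its only power statement concerns the primary outcome. That one is consistent: 100 per arm, 75% against 0.75/1.34 = 56.0%, two-sided alpha 0.05 (assumed, not stated) gives power 0.813 against the stated 0.80. The check of the secondary outcome is therefore mainly a comparison of definitions.

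**Step 1. Scale of the count.** Inputs: SLB is daily and XRB monthly (Differences between SLB and XRB); XRB visits are 28 days apart (XRB maintenance); follow-up is 90 days.

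- SLB, treated throughout: 90 days × 1 per day = 90 doses.
- XRB, treated throughout: if the last jail injection is on the day of release, community injections fall on days 28, 56 and 84, which is 3. If the next one is due on the day of release, they fall on days 0, 28, 56 and 84, which is 4.
- Ratio for equally complete treatment: 90/4 = 22.5 to 90/3 = 30.

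A participant who takes SLB for five days and stops scores 5, above anyone fully treated with XRB.

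**Step 2. The same participant under each form.** The cases are hypothetical.

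| Course after release | Enrolled | Dose/injection count | In buprenorphine treatment at day 90 | In any MOUD at day 90 |
|---|---|---|---|---|
| One intake visit, then stops | Yes | 0 or very low | No | No |
| Moves to methadone at intake, stays to day 90 | Yes | 0 | No | Yes |
| XRB throughout | Yes | 3 or 4 | Yes | Yes |
| SLB for five days, then stops | Yes | 5 | No | No |
| SLB throughout | Yes | 90 | Yes | Yes |

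No two columns order these five people in the same way. The methadone row is realistic: the jail's MATADOR programme offers methadone and naltrexone as well as buprenorphine, and Table 1 records medication type.

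**Step 3. What the choice does to precision (illustration only).** The document's only comparative enrolment figures are the pilot's 69% against 35%, in sentenced participants. Let r be the share of enrollees still in treatment at day 90, assumed equal in both arms. The document gives no value for r. With p1 = 0.69r, p2 = 0.35r, p̄ their mean, n = 100 per arm and two-sided alpha 0.05,

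power = Φ{[(p1 − p2)√n − 1.96√(2p̄(1 − p̄))] / √(p1(1 − p1) + p2(1 − p2))}.

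| r | p1 | p2 | Difference (points) | Power |
|---|---|---|---|---|
| 1 (enrolment) | 0.690 | 0.350 | 34.0 | above 0.99 |
| 0.8 | 0.552 | 0.280 | 27.2 | 0.98 |
| 0.6 | 0.414 | 0.210 | 20.4 | 0.88 |
| 0.4 | 0.276 | 0.140 | 13.6 | 0.66 |

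The risk ratio is 0.69/0.35 = 1.97 in every row because r cancels. The table shows that enrolment and day-90 retention are different targets with different precision. It does not show a change of direction.

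**The case against.** The strongest case against is that the sections can be read together. The outcome section covers admission as well as retention, and the design overview pairs intake with retention, so enrolment belongs to the concept throughout. Planned analyses speaks of outcomes in the plural and says that they include enrolment, which is not exhaustive. The placeholder months stand inside an example of when mixed models apply. Table 1 uses enrolment as a 90-day heading that covers appointments and dose. Exact visit times are normally left to a full protocol or analysis plan.

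Much of this stands, and it rules out three stronger readings.

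- **That the plan scores one intake visit as a success in one place and a failure in another.** The outcome section sets no success rule; such a participant simply gets a low count. The Yes/No sentence says only how participants who were not released are coded in ITT analyses. It does not say that one visit counts as Yes.
- **That enrolment and retention would point in opposite directions.** XRB cover of up to 28 days might delay intake, but the window is 90 days, and nothing in the document shows a reversal. The illustration above cannot show one, because it uses the same r in both arms.
- **That the most favourable version will be reported.** The trial is registered, and neither the registry record nor an analysis plan is at hand. The text supports only the statement that this article leaves the choice open.

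The objection does not reconcile the forms. A non-exhaustive list does not turn a count into a proportion, and reading the sections together does not make daily doses and monthly injections comparable or bring methadone and naltrexone into a count of buprenorphine doses.

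**Conclusion.** The point holds as an inconsistency of definition. The single named secondary outcome has no fixed variable type, drug scope or time point across the outcome section and Planned analyses. The count stated in the outcome section is unsuitable for comparing arms: complete treatment scores 22.5 to 30 times higher on SLB than on XRB, given daily dosing, 28-day intervals and 90 days of follow-up. The size of any effect on the trial's conclusion is unknown, since no retention figure for enrollees is given, and the power figures above rest on assumed shares and a pilot in a different population. The primary outcome and the sample size are not affected. The change is worth making because it is cheap and the outcome cannot be analysed consistently as written.

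**What to change.** Under Secondary and tertiary outcome measures and in both places under Planned analyses, state one secondary outcome in line with 90-day MOUD continuation: in any community MOUD treatment at day 90 after release, yes or no, from clinic records. Analyse it with the log-binomial model already planned for the primary outcome, and state the ITT coding of participants not released in terms of this variable.

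Also:

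- keep enrolment by day 90 as a supportive outcome;
- report dose and injection counts only descriptively and within formulation;
- replace the placeholder months with time points inside follow-up, for example days 30, 60 and 90, which are also the patient navigator's contact times, and say whether that repeated measure covers buprenorphine only or any MOUD.

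The cost is mostly wording. Table 1 already plans clinic records to 90 days, including medication type and number of appointments. It does not list dates, so the data request must ensure that the records show treatment status at day 90. There are two drawbacks. The retention figure will be lower and less precise than enrolment. And a binary status replaces the stated count, so this is a change of metric that should be recorded as such.
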